## Abstract

**Background:**

Cardiogenic shock (CS) is a life-threatening condition characterized by circulatory insufficiency caused by an acute dysfunction of the heart pump. The pathophysiological approach to CS has recently been enriched by the tissue consequences of low flow, including inflammation, endothelial dysfunction, and alteration of the hypothalamic-pituitary-adrenal axis. The aim of the present trial is to evaluate the impact of early low-dose corticosteroid therapy on shock reversal in adults with CS.

**Method/design:**

This is a multicentered randomized, double-blind, placebo-controlled trial with two parallel arms in adult patients with CS recruited from medical, cardiac, and polyvalent intensive care units (ICU) in France. Patients will be randomly allocated into the treatment or control group (1:1 ratio), and we will recruit 380 patients (190 per group). For the treatment group, hydrocortisone (50 mg intravenous bolus every 6 h) and fludrocortisone (50 μg once a day enterally) will be administered for 7 days or until discharge from the ICU. The primary endpoint is catecholamine-free days at day 7. Secondary endpoints include morbidity and all-cause mortality at 28 and 90 days post-randomization. Pre-defined subgroups analyses are planned, including: postcardiotomy, myocardial infarction, etomidate use, vasopressor use, and adrenal profiles according the short corticotropin stimulation test. Each patient will be followed for 90 days. All analyses will be conducted on an intention-to-treat basis.

**Discussion:**

This trial will provide valuable evidence about the effectiveness of low dose of corticosteroid therapy for CS. If effective, this therapy might improve outcome and become a therapeutic adjunct for patients with CS.

**Trial registration:**

ClinicalTrials.gov, NCT03773822. Registered on 12 December 2018

## Background

Cardiogenic shock (CS) is a serious condition characterized by circulatory insufficiency caused by an acute dysfunction of the heart pump. The prognosis of critically ill patients with CS has relatively improved over these last decades [1], thanks to recent progress [2], like early myocardial revascularization during myocardial infarction [3]. Nevertheless, the early mortality rate remains unacceptably high, around 45% [1, 2].

The pathophysiology of CS has recently evolved with a new hemodynamic paradigm [4] involving sepsis-like alterations, with the tissue consequences of low flow, including inflammation, endothelial dysfunction, and alteration of the hypothalamic-pituitary-adrenal (HPA) axis. Critical illness-related corticosteroid insufficiency (CIRCI) was first described in septic shock [5] and is characterized by a functional impairment of the HPA axis during various critical illnesses [6]. Corticosteroids have pleiotropic effects including immune modulation, metabolic, and cardiovascular effects. The results of studies testing corticosteroid supplementation in septic shock were controversial in terms of mortality [7–10], but most of them demonstrated that corticosteroid therapy accelerates reversal of shock. Two large recent trials (ADRENAL [11] and APROCCHSS [12]) confirmed a faster reversibility of septic shock with low-dose steroids. The latest study further demonstrated a decrease in mortality in the group receiving a combination of fludrocortisone and hydrocortisone in adult patients with severe septic shock.

During septic shock, CIRCI seems to be more prevalent in patients with myocardial dysfunction as compared to those with normal cardiac function [13]. CIRCI has recently been found in patients with CS and associated with a worse prognosis in this setting [14, 15]. However, no study has evaluated the effect of corticosteroid supplementation in CS.

Although the survival could be a more robust primary endpoint, it seemed unreasonable for the present study given the small difference in mortality expected based on septic shock studies. A composite endpoint including mortality and shock reversal seemed more appropriate.

## Objective

The “low dose COrticosteroids for Cardiogenic shoCk in Adult patients” (COCCA) trial is designed to evaluate the hemodynamic effects of early low-dose corticosteroid therapy (with hydrocortisone and fludrocortisone) on CS reversal, as defined by catecholamine-free days at day-7.

## Method

### Study design

The COCCA trial is a nationwide multicenter, randomized, double-blind, placebo-controlled trial, with 2 parallel arms.

### Ethical consideration and clinical trial authorization

This study follows the principles of the current version of the Helsinki Declaration, the French Law on Protection of Personal Information and the National Health Law. The whole protocol has been reviewed and approved by an Independent Ethics committee (Comité de Protection des Personnes CPP— Ile-de-France IV, number 2018/40) and the French health authorities (Agence Nationale de Sécurité du Médicament, on September 3, 2018, number EudraCT 2018-000729-30). The trial was registered at ClinicalTrials.gov on December 12, 2018, before inclusion of the first patient, under the number NCT03773822.

### Participating centers

Participating centers include French university and non-university hospitals, all with a cardiac and a medical intensive care unit (ICU) and all with a high volume of patients with CS. List of the participating centers is provided in Additional file 1.

### Participants

Eligible patients are all consecutive adult patients who are admitted to the participating ICUs for CS. Complete eligible criteria are shown in Table 1. All eligible patients will be included in the study after obtaining signed informed consent or adapted procedure as per French law. In practice, the consent will be obtained as follows:

**Table 1 Tab1:** Eligibility criteria

Inclusion criteria	Exclusion criteria
1. Adult (age **≥** 18 years);	1. Cardiogenic shock state with catecholamine infusion for more than 24 h;
2. Cardiogenic shock state according to the following definition:	2. Presence of sepsis at inclusion;
a. Systemic arterial hypotension (SAP < 90 mmHg or MAP < 65 mmHg for 30 min) and/or low cardiac output requiring catecholamines to achieve a systolic blood pressure ≥ 90 mmHg;	3. Cardiac arrest recovered within 7 days prior to inclusion, with at least one of the following early signs of poor prognosis: no witness, non-shockable rhythm, CAHP score > 150 [16];
a. Sign of hypocontractility or low cardiac output among the following: cardiac index ≤ 2.2 L/min/m^2^, left ventricular ejection fraction (LVEF) ≤ 40%, or VTI LVOT ≤ 18 cm, or need for catecholamines to maintain adequate cardiac index, LVEF, or VTI LVOT;	4. Patients already on MCS before inclusion;
b. Signs of impaired organ perfusion with at least one of the following criteria:	5. Cardiogenic shock cause by viral myocarditis;
**i**. Altered mental status	6. Corticosteroid therapy within 4 weeks prior to inclusion;
**ii.** Skin mottling	7. Patient receiving one of the following treatments: ketoconazole, rifampicin, phenytoin, phenobarbital, cyclosporine, clarithromycin;
**iii.** Oliguria (≤ 25 ml/h)	8. Hypersensitivity to fludrocortisone or hydrocortisone;
**iv.** Increased serum lactate (> 2 mmol/L)	9. Pregnancy or breastfeeding;
c. Pulmonary congestion or elevated left-ventricular filling pressures	10. Privation of liberty by administrative or judicial decision;
3. Written informed consent from the patient or proxy (if present) before inclusion or once possible when patient has been included in a context of emergency;	11. Refusal of study participation or to pursue the study by the patient;
4. Benefiting of coverage by the French statutory healthcare insurance system.	

*SAP* systolic blood pressure, *MAP* mean arterial pressure, *CAHP* Cardiac Arrest Hospital Prognosis, *VTI LVOT* velocity-time integral of left ventricular outflow tract, *MCS* mechanical circulatory support

1. If the patient is capable of participating in the consent process, the investigator will obtain a written consent from the patient.

2. If the patient is unable to give his consent (e.g., comatose), the investigator will obtain a written consent from his/her legally acceptable representative as per French law. As soon as the patient will be capable of participating in the consent process, he will be given full information about the study and the investigator will obtain a continuation consent from the patient.

3. If the patient is not capable of participating in the consent process, and his/her legally acceptable representative is not present at the time of selection criteria fulfillment, the patient will be included in emergency situation as per French law. The patient or, where applicable, his/her legally acceptable representative shall be informed as soon as possible and their consent shall be sought for the possible continuation of such research.

### Randomization, comparator, and blinding

Randomization will be centralized, through a secured website, and will be stratified according to center, using permutation blocks whose size will be unknown by investigators. Patients will be randomly allocated to receive hydrocortisone plus fludrocortisone, or placebos of hydrocortisone and fludrocortisone, with double blinding. The consecutive 24 h before and after the randomization will be considered as study day-0 and day-1, respectively.

The drugs will be prepared prior to the initiation of the study and will be packed by the Pharmacology Department, *CMC Ambroise Paré*, according to the randomization list. Treatment boxes will be coded and masked centrally. Corticosteroids or placebos will be sealed in sequentially numbered, identical boxes containing 30 vials of lyophilized hydrocortisone or its placebo and 30 ampoules of injectable water and a blister package with 10 tablets of fludrocortisone or its placebo. Each box will be provided with a detachable sticker for traceability.

This study is a double-blind study: participants, clinicians, and researchers (outcome assessors and statistical analysts) are blinded to the group assignment and the blindness will never be broken prior to the completion of study unless in particular conditions. Indeed, unblinding should only be requested by the treating physician in the context of a medical emergency, when knowledge of the allocated treatment is necessary for the management of the patient.

### Withdrawal or dropout criteria

Interventions in either active group or control group will be stopped if participants meet the following criteria: (1) subject is unwilling to continue the intervention for any reasons and (2) subject suffers from any suspected unexpected serious adverse reaction during the intervention period.

### Study interventions

The study flow chart is shown in Fig. 1. Immediately after randomization, and before study drug administration, a short corticotropin stimulation test and an echocardiographic assessment will be performed, if possible.

**Fig. 1 Fig1:**
[figure not shown]
Study flow chart

Patients will be randomized to intravenous infusion of hydrocortisone (50 mg/6 h) for 7 days or until discharge from the ICU, according to which event occur first) with enteral administration of fludrocortisone (tablet of 50 μg once daily in the morning for 7 days or until discharge from the ICU, according to which event occurs first) or to respective placebos. Active and placebo drugs have similar aspects.

Co-interventions will be standardized according to the French recommendations for the management of adult patients with CS [17]. The current standard is administered to both groups in addition to the intervention and placebo. Blood glucose levels will be monitored at least every 8 h and maintained at ≤ 150 mg/dl by intravenous infusion of insulin. Administration of sedative and analgesic drugs or muscle relaxants is left at the discretion of the clinician. A protocol for catecholamine weaning will be suggested to all centers in order to standardize practices. Centers where a local protocol is already in use will be authorized to continue using it. Open-labeled corticosteroids will be discouraged and no treatment will be prohibited. If there is a formal indication for corticosteroid therapy during the experimental treatment, this should be notified and justified.

### Cortisol assays

The short corticotropin stimulation test will be performed by injecting 250 mg of tetracosactrin (Synacthen®, Ciba, Reuil-Malmaison, France) intravenously as described previously [14]. The maximal post stimulation cortisol concentration (*T*_max_) is the highest value between *T*_30_ and *T*_60_. The maximal cortisol response (Δ_max_) is defined as the difference between *T*_max_ and the baseline cortisol concentration (*T*_0_). CIRCI is defined as *T*_0_ < 10 μg/dL (276 nmol/L) and/or Δmax < 9 μg/dL (248 nmol/L) [18]. We will define nonresponders to the corticotropin stimulation test as patients with Δmax < 9 μg/dL, whatever the baseline cortisol [19, 20].

## Catecholamine management

### Vasopressors

The management of vasopressors will be guided by a mean arterial pressure (MAP) target of 65–70 mmHg; this target can be individualized by the attending physician according to the patient's history (e.g., chronic arterial hypertension). In practice, as soon as MAP > 70 mmHg, it is recommended to decrease the vasopressor infusion rate in decrements of 0.05 μg/kg/min, at least every hour. If MAP > 75 mmHg, the vasopressor infusion rate is decreased in decrements of 0.1 μg/kg/min, at least every hour. In the event of hypotension or sign of impaired organ perfusion during vasopressor weaning, a return to the previous level and hemodynamic exploration will be suggested [21].

### Inotropes

The management of inotropes will be guided by cardiac index and correction of signs of hypoperfusion (e.g., mottling, oliguria < 25 ml/h, altered state of consciousness, hyperlactatemia > 2 mmol/L, central venous oxygen saturation < 60%). In practice, as soon as the tissue perfusion target is reached (and in the absence of hypotension), a decrease in dobutamine dose of 2.5 μg/kg/min will be suggested every 4 to 12 h, based on clinical evaluation. In the event of hypotension or tissue hypoperfusion during weaning, a return to the previous level and hemodynamic exploration will be suggested.

## Data collection and follow-up

Patients will be followed for 90 days (Table 2). In the data collection process, each patient is assigned a code. Data will be collected by electronic case report forms (eCRF) compliant to good clinical practice (GCP) and will be recorded on a central, secure server. Data entry will be managed by assessor blinded. Besides, each eCRF will be checked to ensure the accuracy and completion of data collection throughout the study. All personal information about potential and enrolled participants will be confidential.

**Table 2 Tab2:** Enrollment, intervention, and evaluations

Time points	ICU admission to enrollment	Experimental period							Early follow-up (D7 or ICU discharge)	Follow-up	Close out
	D0	D1	D2	D3	D4	D5	D6	D7	Dx	D28	D90 + 20 days
*Enrollment*											
Eligibility screen	**•**										
Informed consent	**•**										
Randomization	**•**										
*Intervention*											
Physical examination	**•**	**•**	**•**	**•**	**•**	**•**	**•**	**•**			
Biology exams	**•**	**•**	**•**	**•**	**•**	**•**	**•**	**•**			
Echocardiography	**•**		**•**						**•**		
Corticotropin stimulation test	**•**										
Treatment		**•**	**•**	**•**	**•**	**•**	**•**	**•**			
*Assessments*											
Collection of data on the occurrence of primary endpoint									**•**		
Collection of data on the occurrence of secondary endpoints									**•**	**•**	**•**
Serious adverse events		**•**	**•**	**•**	**•**	**•**	**•**	**•**	**•**	**•**	**•**

### Baseline

Baseline data will include the following: (1) demographic and anthropometric data; (2) type of consent; (3) time of hospital and ICU admissions; (4) medical history (chronic heart failure and its cause, cardiac surgery, pacemaker, arterial hypertension, dyslipidemia, smoking, chronic obstructive pulmonary disease, chronic dialysis…); (5) etiology of CS and ventricle affected; (6) severity of illness using vital signs, Simplified Acute Physiology Score (SAPS) II [22] and sequential organ failure assessment (SOFA) score [23]; (7) type and dose of vasopressors and inotropic drugs, fluid infusion; (8) time from shock onset; (9) biological data, blood gas analyses and arterial lactate levels; (10) treatments used before randomization (etomidate, insulin, anticoagulant and antiplatelet therapies, diuretics, proton pump inhibitor, beta-blockers, mineralocorticoid receptors antagonist, renin angiotensin system inhibitors, amiodarone, levothyroxine and sedatives); (11) ventilation mode; and (12) results of the corticotropin stimulation test (baseline cortisol and Δmax).

### During treatment

We will record on a daily basis, from day 1 to day 7 or ICU discharge the following variables: (1) vital signs; (2) biological data, blood gas analyses and arterial lactate levels; (3) SOFA score [23]; (4) type and dose of vasopressor and inotropic drugs, fluid infusion; (5) other treatments used (insulin, diuretics, sedatives); (6) episodes of hyperglycemia (> 150 mg/dl); (7) administration of study drugs (hydrocortisone and fludrocortisone or placebos) and reason if it stopped; and (8) type, dose, and reason for use of any open-labeled corticosteroids.

### Echocardiographic evaluations

When possible, patients included will undergo echocardiographic assessment at randomization, day 2 and day 7 (or ICU discharge) to assess the hemodynamic changes caused by low-dose steroids with the following variables: (1) left ventricular systolic function with left ventricular ejection fraction (LVEF), systolic velocity at the mitral annulus (S-mit) and left ventricular global longitudinal strain by speckle-tracking; (2) cardiac index, obtained by measuring the velocity-time integral of left ventricular outflow tract; (3) estimation of left ventricle filling pressures, using pulsed-wave Doppler early (E) and late (A) diastolic wave velocities at the mitral valve, and tissue Doppler early (e’) diastolic wave velocity at the lateral mitral valve annulus; and (4) right ventricular function as reflected by tissue Doppler peak systolic wave at the lateral tricuspid annulus (S-tric), tricuspid annular plane systolic excursion, and estimation of systolic pulmonary arterial pressure.

### Follow-up

At day 28 and day 90, the following data will be recorded: (1) recurrence of shock (with new vasopressor and/or inotropic support); (2) mechanical circulatory support (MCS) and cardiac transplantation; (3) mechanical ventilation (MV) ; (4) specific treatment for CS (coronary reperfusion by percutaneous coronary intervention, fibrinolytic therapy, or cardiac surgery, vale replacement or repair, catheter ablation of arrhythmias, cardioversion, defibrillator or pacemaker implantation and pericardial drainage); (5) nosocomial infections; (6) renal replacement therapy; (7) other complications (bleeding, stroke, delirium, ICU-acquired neuromuscular weakness, (8) hospital and ICU length of stay; and (9) hospital and ICU mortality. Adverse events and complications will be assessed systematically.

## Endpoints

Catecholamine-free days at day 7 will be the primary endpoint. Secondary endpoints will include the following: (1) mortality at ICU and hospital discharge, day 28 and day 90; (2) ICU and hospital length of stay (days) [time frame: 28 and 90 days after randomization]; (3) total duration of catecholamine infusion (days) [time frame: 28 days after randomization] [24]*;* (4) number of days alive (up to day 28 and day 90) and free of catecholamines; (5) rate (%) of patients with need of MV [time frame: 28 days after randomization]; (6) rate (%) of patients with need of MCS [time frame: 28 days after randomization]; (7) number of days alive (up to day 7, day 28, and day 90) and without cardiovascular failure (as defined by a cardiovascular SOFA score < 3) [time frame: 7 days after randomization]; (8) lactate clearance (mmol/L) [time frame: 7 days after randomization]; (9) change in mean arterial pressure (mmHg) from the baseline [time frame: 7 days after randomization]; (10) change in cardiac index (L/min/m^2^) [time frame: 7 days after randomization]; (11) rate (%) of patients with nosocomial infection [time frame: 28 days after randomization]; (12) rate (%) of patients with need of intravenous insulin therapy [time frame: 7 days after randomization]; and (13) rate (%) of other adverse effects of corticosteroid treatment (hyperglycemia, gastrointestinal bleeding, stroke, delirium, ICU-acquired neuromuscular weakness, significant hypokalemia or hypernatremia) [time frame: 28 days after randomization].

## Subgroup analysis

We plan to explore treatment effects according to the following parameters: (1) CS secondary to acute myocardial infarction, (2) or postcardiotomy, (3) etomidate use, (4) vasopressor support, and (5) adrenal profiles (CIRCI and nonresponders to corticotropin stimulation test) [14, 18, 25].

## Sample size and statistical analysis

Based on literature [14], the primary endpoint (catecholamine-free days at day 7) is estimated at 3 ± 3 days. The increase in this number of days reasonably expected in the corticosteroid group is + 1 day [11, 12, 19]. With a bilateral formulation, 190 patients will be needed in each group (total of 380 patients), with a statistical power of 90% and an α risk of 5% to conclude to the efficacy of the experimental group.

An intention-to-treat (ITT) and a per-protocol (PP) analysis will be performed. Following the ITT principle, all randomized patients receiving at least one dose of study medication will be included in the analysis with group allocation as randomized. The PP population will be composed of patients included in the study, without major deviations from the protocol, including erroneous inclusion of patients not meeting all selection criteria, modifications or non-compliance with the initial allocated treatment, and appearance of a formal indication for corticosteroid therapy during experimental period. The primary endpoint analysis will be performed on the ITT population. Additional analyses of the primary endpoint and all secondary endpoint analyses will be performed on both the ITT and PP populations in order to describe patients excluded from the PP population and assess the impact on the ITT analysis and the robustness of the results obtained.

Any missing or invalid data will be systematically checked and searched for in the medical records of the patient concerned. In addition to the analyses of complete cases without missing data for the primary endpoint, sensitivity analyses will be performed using several methods of replacing missing data, including the Last Observation Carry Forward (LOCF) method, the worst-case scenario assumption, and multiple imputation chain equation (MICE) techniques. There are no plans to replace subjects who left the study prematurely.

No intermediate analysis is planned. STATA v14.1 (Stata Corp, College Station, TX, USA) and R 3.2.4 (R Foundation for Statistical Computing, Vienna, Austria) will be used for data analysis. The primary endpoint will be catecholamine-free days at day 7. The analysis of the primary endpoint will be carried out on the ITT population. Additional sensitivity analyses will be conducted on the PP population. Descriptive analyses will be performed. Normally distributed variables will be expressed as mean and standard deviations; non-normally distributed variables will be expressed as medians and inter quartile ranges. For categorical variables, number of patients in each category and corresponding percentages will be given. The effects of treatments on mortality rates will be compared using a logistic regression. Cumulative event curves (censored endpoints) will be estimated with Kaplan–Meier procedure, and Cox model will be used to compare treatments effects. Analysis of variance will be used to compare number of days alive and free of vasopressors, MV, and with a cardiovascular SOFA score < 3. The same analyses will be conducted for subgroups unless the numbers of patients are insufficient. In this case, statistical methods will be adapted according to sample sizes.

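### The analysis of variance is assigned to vasopressor-free days, whereas the powered endpoint is catecholamine-free days; the centre term should also be stated

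*Protocol article*

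**What the plan says.** All places are in the protocol article.

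- **Endpoints:** "Catecholamine-free days at day 7 will be the primary endpoint". A secondary endpoint is the "number of days alive (up to day 28 and day 90) and free of catecholamines". Vasopressor-free days is not listed.
- **Sample size and statistical analysis:** the trial is powered on catecholamine-free days at day 7. The section repeats that this is the primary endpoint and is analysed by intention to treat. The only method it names for any free-days outcome is: "Analysis of variance will be used to compare number of days alive and free of vasopressors", together with days free of mechanical ventilation and days with a cardiovascular SOFA score below 3. Mortality is assigned to logistic regression and censored endpoints to a Cox model. No model terms are listed for any of these.
- **Randomization, comparator, and blinding:** allocation "will be stratified according to center, using permutation blocks whose size will be unknown by investigators". Centre is the only stratification factor.
- **Study interventions:** a catecholamine weaning protocol is suggested to all sites, but "Centers where a local protocol is already in use will be authorized to continue using it".
- **Baseline:** SOFA, SAPS II, arterial lactate and the "type and dose of vasopressors and inotropic drugs, fluid infusion" are all recorded.

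**The concern.** **Outcome named in the test.** The article does not use the two terms interchangeably. Catecholamine management has one subsection for vasopressors and another for inotropes, the latter built around dobutamine. The daily record lists the two drug classes separately. Vasopressor support is a planned subgroup, which makes sense only if some enrolled patients receive none. The two variables can therefore differ within a patient. Left as it stands, the sentence allows a choice of outcome variable, or of test for the primary endpoint, after the data are seen.

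**Centre.** Weaning practice acts directly on the primary endpoint, and sites may keep local weaning protocols, so differences in outcome between centres are plausible. When allocation is balanced within centres, an analysis without a centre term leaves between-centre variance in the error term. The reported standard error is then larger than the true one.

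**Working it through.** **1. Which variable the test applies to**

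| Place | Variable |
|---|---|
| Endpoints, primary | catecholamine-free days, day 7 |
| Endpoints, secondary | days alive and free of catecholamines, days 28 and 90 |
| Sample size | catecholamine-free days, day 7 |
| Analysis of variance sentence | days alive and free of vasopressors |

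A patient alive and on dobutamine alone from day 1 to day 7 scores 0 catecholamine-free days but 7 vasopressor-free days. Such patients can be enrolled: the eligibility table admits low cardiac output requiring catecholamines as an alternative to hypotension. Their number is not given, so the average gap between the two variables cannot be calculated.

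**2. The plan's own sample size**

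Inputs from the statistical section: difference 1 day, SD 3 days, two-sided alpha 5%, power 90%.

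n per arm = 2 × SD² × (1.960 + 1.282)² / difference² = 2 × 9 × 10.51 / 1 = 189.2, rounded up to 190.

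This reproduces the stated 190 per arm; power at 190 is 90.1%. The calculation has no centre or covariate adjustment. That fits an unadjusted analysis but does not show that one is planned.

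**3. What omitting centre would do**

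Let r be the share of outcome variance that lies between centres. The article text gives no r, so a range is assumed.

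- Reported SE without centre: 3 × √(2/190) = 0.308, so difference/SE = 3.25.
- True SE under within-centre balance: 0.308 × √(1 − r).
- Actual alpha, unadjusted: 2 × [1 − Φ(1.96/√(1 − r))].
- Power, unadjusted: Φ((3.25 − 1.96)/√(1 − r)).
- Power, adjusted: Φ(3.25/√(1 − r) − 1.96).
- 95% CI half-width: 1.96 × SE, which is 0.603 day unadjusted.

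| Assumed r | Reported/true SE | Actual alpha, unadjusted | Power, unadjusted | Power, adjusted | Half-width, adjusted (days) |
|---|---|---|---|---|---|
| 1% | 1.005 | 4.9% | 90.2% | 90.4% | 0.600 |
| 5% | 1.026 | 4.4% | 90.7% | 91.5% | 0.588 |
| 10% | 1.054 | 3.9% | 91.3% | 92.9% | 0.572 |
| 15% | 1.085 | 3.4% | 91.9% | 94.1% | 0.556 |

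The power gained by adjusting is the difference within a row: 0.2, 0.8, 1.6 and 2.2 percentage points.

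A simulation (assumed 20 centres of 19 patients, blocks of 4, 4000 runs) gave unadjusted type I error of 5.2%, 4.3% and 3.0% at r = 5%, 10% and 20%. With centre in the model it gave 5.7%, 5.3% and 5.0%. The Monte Carlo standard error is about √(0.05 × 0.95/4000) = 0.3 points. The conservatism is clear at 10% and 20%; at 5% the simulated rate is close to nominal.

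**4. Baseline severity**

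Severity is not a stratification factor, so the unadjusted standard error remains valid and power stays at 90.1%. Covariates explaining an assumed 5%, 10%, 20% or 30% of variance would raise power to 91.5%, 92.9%, 95.3% or 97.3%. Omitting them costs precision only.

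**The case against.** The strongest objection concerns centre. The article names types of model and lists no terms; an analysis of variance can carry a centre factor. Model terms are commonly left to the full protocol or the analysis plan, neither of which is shown. A reader might infer that the plan ignores centre and baseline severity. The text does not support that: it neither includes nor excludes them. The article also suggests a common weaning protocol and common targets, so centre differences may be small, and at r = 1% the effect is negligible. All of this stands and limits the centre point to a request to state the term.

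A reader might also infer that the intervals are invalid. They would be affected only if centre is left out and outcomes differ between centres, and then they would be slightly too wide. Nor should adjusted power be set against the planned 90%. Unadjusted power under stratification already rises with r, and the naive comparison roughly doubles the gain.

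On the outcome wording, it can be said that the endpoint itself is not in doubt. The article consistently names catecholamine-free days as primary, and the analysis of variance sentence is not labelled the primary analysis. That is fair, but it does not remove the mismatch: the one sentence assigning a test to free-days outcomes names a variable absent from the endpoint list. This is a contradiction in the published text, not an omission that another document could be presumed to fill.

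**Conclusion.** The point holds, led by the outcome mismatch. The test is attached to vasopressor-free days while catecholamine-free days are defined and powered, and the article's own distinction between vasopressors and inotropes means the two are not the same. This is a problem of endpoint definition; it does not itself cause any loss of precision or faulty interval.

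The centre point is secondary and conditional. If centre were omitted, and for an assumed variance share of 1% to 15%, intervals would be 0.5% to 8.5% too wide, alpha would fall to between 4.9% and 3.4%, and 0.2 to 2.2 points of power would be given up. Power stays above the planned 90% throughout and no false-positive risk is added. These figures rest on the assumed variance shares and on allocation being balanced within centres. The stated 190 per arm is correct for its inputs and does not need to change.

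**What to change.** In the statistical section:

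1. Replace vasopressors by catecholamines, defined as vasopressor or inotrope, in the analysis of variance sentence, and name this analysis as the primary test for catecholamine-free days at day 7.
2. Specify the primary analysis as a linear model with treatment and centre, with centre as a random effect or with small centres pooled.
3. Optionally add a few baseline covariates fixed in advance from those already collected, for example SOFA, lactate and catecholamine dose.
4. Keep the unadjusted analysis of variance as a sensitivity analysis.

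If the full protocol or analysis plan already contains these terms, it is enough to align the wording. The cost is text only: no new data and no change in sample size. It should be done before unblinding.
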